
#### Sample Size

As per good research practices, the sample sizes for utility estimates should be based on precision rather than hypothesis testing [38,43]. Indeed, there is no consensus on the use of minimally important differences in EQ-5D measures for statistical power calculations [31,44]. Therefore, the sample size was determined to ensure reasonable variability around the utility value for SHEs (which also ensures precision for NSHEs as the incidence is significantly higher). However, no value for the expected SD was found in the literature for performing a reliable precision-based sample size calculation. A literature review was performed to identify studies that estimated utility values for hypoglycemia. However, it is often difficult to find an expected SD for utility values because they are sensitive to the type of instrument, country, precise definition of outcome, or timeframe. Furthermore, most studies did not provide uncertainty values around the estimates. As discussed by Beaudet et al [4], utility values for hypoglycemia are limited and CIs are scarce.

Therefore, the required sample size was determined based on the study by Currie et al [5], which is used as a reference for hypoglycemic utility values by CADTH and NICE [6,7]. Currie et al [5] obtained utility estimates from 68 patients who experienced at least one SHE over a 3-month period. According to Canadian real-world studies, the 3-month incidence of SHEs among insulin-treated patients with T2DM was approximately 17% [18,19,45]. With a 3-month incidence rate of 17%, 400 patients will have to be recruited to ensure that 68 patients experience at least one SHE during the study follow-up. To account for attrition, the sample size will be increased by 20% for a target number of 500 enrolled patients. It is assumed that this sample size will also ensure the precision of the productivity estimates.

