**Methods:**

This noninterventional, multicenter, 3-month prospective study will recruit patients from 4 medical clinics and 2 endocrinology or diabetes clinics. Patients will be identified using appointment lists and enrolled through consecutive sampling during routinely scheduled consultations. To be eligible, patients must be aged ≥18 years, diagnosed with T2DM, and treated with insulin. Utility and productivity will be measured using the EQ-5D-5L questionnaire and Institute for Medical Technology Assessment Productivity Cost Questionnaire, respectively. Questionnaires will be completed 4, 8, and 12 weeks after recruitment. Generalized estimating equation models will be used to investigate productivity losses and utility decrements associated with incident hypoglycemic events while controlling for individual patient characteristics. A total of 500 patients will be enrolled to ensure the precision of HEOR estimates.

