## Methods

### Research Purpose and Study Design

This noninterventional, multicenter, 3-month prospective study is designed to collect HEOR inputs for future economic modeling. This study will generate descriptive HEOR estimates that can be incorporated into T2DM models, along with precision parameters (ie, CIs and SEs) to evaluate uncertainty in CUAs in sensitivity analyses. Considering the nature of the disease, a longitudinal design with repeated measures was deemed appropriate to limit confounding and increase the quality of evidence.

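### The sample size is said to guarantee 68 patients with a severe hypoglycemic event (SHE), but 68 is only the expected number; the target of 500 is right but is wrongly described as a 20% increase

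*Protocol article*

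**What the plan says.** The Sample Size section first sets out the principle that "the sample sizes for utility estimates should be based on precision rather than hypothesis testing". It then reports that no usable SD was found in the literature and takes a count from the reference utility study instead. That study "obtained utility estimates from 68 patients who experienced at least one SHE over a 3-month period". Canadian real-world studies are cited to show that "the 3-month incidence of SHEs among insulin-treated patients with T2DM was approximately 17" percent. From these two figures the section concludes that "400 patients will have to be recruited to ensure that 68 patients experience at least one SHE during the study follow-up".

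The attrition step follows: "To account for attrition, the sample size will be increased by 20% for a target number of 500 enrolled patients". The Methods paragraph of the Abstract carries the same assurance in broader form: "A total of 500 patients will be enrolled to ensure the precision of HEOR estimates".

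**The concern.** Two statements do not match the arithmetic beneath them.

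- **The guarantee.** Dividing a target count by an incidence gives the number of patients at which that count is expected on average. It does not give the number at which the count is assured.
- **The percentage.** A 20% increase on 400 is not 500.

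The first matters more. The count of 68 is the only quantitative support for the sample size. It stands in for a precision calculation that could not be done. Precision for nonsevere events is inferred from it, and precision for productivity is assumed to follow. The study's declared purpose is to supply estimates with SEs and CIs for economic models, so readers will rely on what the article says about precision. The second is a misdescription that stops a reader from reproducing the target from the stated rule.

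**Working it through.** **Inputs, all from the Sample Size section:** target count 68; 3-month SHE incidence about 17%; 400 patients before attrition; 20% attrition allowance; 500 enrolled.

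**1. Reproduce the 400.** 68/0.17 = 400, or equally 400 × 0.17 = 68. The figure reproduces, and 68 is the mean of the count.

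**2. Reproduce the 500.**
- Dividing by the retained fraction: 400/(1 − 0.20) = 400/0.80 = 500. This reproduces exactly.
- A literal 20% increase: 400 × 1.20 = 480. This does not.
- 500/400 = 1.25, so the step is a 25% increase, which is what an allowance for 20% attrition requires.

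**3. Chance of reaching 68.** Let X be the number of followed patients with at least one SHE, with X ~ Binomial(n, 0.17) and patients independent.

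| Situation | Followed (n) | Expected | P(X ≥ 68) |
|---|---|---|---|
| Full 20% of 500 lost, as planned | 400 | 68.0 | 0.521 |
| Half of that loss (assumption) | 450 | 76.5 | 0.87 |
| No loss | 500 | 85.0 | 0.984 |

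For n = 400 the 2.5% and 97.5% points of the binomial are 54 and 83. Letting attrition vary at random, so that each of the 500 is retained with probability 0.80 and has an SHE with probability 0.17, gives a per-patient probability of 0.80 × 0.17 = 0.136 and P(X ≥ 68) = 0.520. The attrition allowance therefore adds no margin if the planned 20% is lost.

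**4. Sensitivity to the incidence.** The article gives 17% as approximate and without a range. Taking one percentage point either way, purely as an assumption and with 400 followed: at 16%, 64 expected and P(X ≥ 68) = 0.31; at 18%, 72 expected and P = 0.72.

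**5. What a shortfall would cost.** With no SD in the document, an absolute CI width cannot be computed. If the SE scales as 1/√n in the number of patients with an SHE (an assumption), then 54 instead of 68 multiplies the CI width by √(68/54) = 1.12, about 12% wider. This is a rough guide only, because the model enters events as a log-transformed count and not as any versus none.

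**The case against.** The strongest reply is that 68 is a benchmark borrowed from another study, not a threshold. Nothing in the plan succeeds or fails at 68, and precision falls gradually: the lower end of the 95% range costs about 12% in CI width. This stands. A reader might infer from the 52% that the study has an even chance of failing, and the document does not support that. What remains is that the text claims an assurance that its own calculation does not provide.

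A second reply is that the 52% assumes the worst use of dropouts. The Missing Data section plans an available-case GEE, or a weighted GEE, so a patient lost after week 4 or week 8 still contributes earlier assessments and any SHE reported in them. This also stands. The chance lies somewhere between 52% and 98%, depending on how much follow-up is lost.

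A third reply is that 500 is correct. It is. A reader might infer from the words about a 20% increase that the target should be 480, or that recruitment could stop there. The same sentence and the Abstract both fix 500, so neither follows.

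It is also tempting to argue that three 28-day recalls cover 84 days and that 17% should be scaled down. The Strengths and Limitations section treats three 4-week assessments as 3 months, and the cited studies, which are not available here, may have used the same window. That adjustment has no basis in the document. Nor is there a source for materially lower incidences.

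**Conclusion.** The point holds as a matter of wording. At 17% incidence with 400 patients followed, 68 is an expectation that is met or exceeded about 52% of the time (95% range 54 to 83). With all 500 followed, 85 are expected and the chance is about 98%. These figures rest on the stated incidence and on independence between patients. The 52% also requires that the full 20% is lost and contributes no SHE data.

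The target of 500 is right, and only its description as a 20% increase is wrong. A reader might go further and ask for a larger sample. The document does not support that: it sets no probability of reaching 68 and no precision target against which 500 could be judged too small. The correction is still worth making, because this is the article's only numerical argument for the sample size.

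**What to change.** In the Sample Size section, replace the guarantee and the attrition sentence with text such as:

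> With 500 enrolled and 20% attrition (400/0.80 = 500), 68 patients with at least one SHE are expected at a 3-month incidence of 17% (95% range 54 to 83; about a 52% chance of at least 68).

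In the Methods paragraph of the Abstract, replace the claim that enrolling 500 ensures precision with one that the number was chosen so that about 68 patients with an SHE are expected.

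Optionally, add a sentence labelled as an assumption: if the SE scales as 1/√n, having 54 rather than 68 such patients would widen the CI by about 12%. An absolute precision figure should not be asked for, since no SD is available.

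The cost is two edits to the text. The stated assurance becomes more modest; enrolment, design and analysis do not change.

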#### Missing Data

Missing data will be defined according to outcome-specific guidelines, and a descriptive analysis will be conducted. According to the EQ-5D guidelines, situations that should be treated as missing data include not only unit nonresponse (no completion of questionnaire) but also item nonresponse (incomplete questionnaire) and ambiguous values (eg, 2 boxes are ticked for a single dimension). When completing the *i*PCQ, some questions can be skipped if they are not applicable (eg, when the patient is not employed). If the questions necessary to score a module are incomplete, the module is defined as missing.

If ≤5% of the data are missing and there is no significant difference between completers and noncompleters, missing data will be assumed to be missing completely at random (MCAR). Under the MCAR assumption, the available case analysis performed with a GEE model yields valid estimates [40,46-48]. If >5% of the data are missing, the missing data pattern will be categorized as monotonic (ie, no return after dropout) or nonmonotonic (ie, intermittent missing data). Moreover, the mechanism by which data are missing will be investigated by examining which baseline covariates and previous measurements predict the missingness of a given outcome. On the basis of the results of the regression analysis, a specific variable will be determined to be a predictor of missingness based on statistical significance and clinical plausibility [49]. In the presence of predictors of missingness, data will be considered as not MCAR, which may bias the GEE estimates. This would lead to the use of the weighted generalized estimating equation (WGEE), a recently published extension of the GEE that incorporates an inverse probability weight matrix [50]. WGEE is a valid approach for dropout missingness (monotonic missing pattern), which is the typically observed pattern in longitudinal HEOR studies [51]. In addition, HEOR outcomes are most commonly missing as unit nonresponses (no completion of questionnaire) rather than item nonresponses (incomplete questionnaire) [49,51]. Therefore, the overall questionnaire scores (eg, EQ-5D index score) will be used for missing data analysis. If the use of the WGEE is required, a sensitivity analysis will be conducted to compare the WGEE results with the GEE estimates for the available case analysis.

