#### Assessments and Study Calendar

Patients will complete a self-assessment questionnaire (SAQ) at 4, 8, and 12 weeks to report the number of NSHEs and SHEs experienced in the last 28 days. Patients will also be provided with a diary to prospectively record hypoglycemic events. Both the SAQ and the diary will be used to estimate the number of hypoglycemic events. The EQ-5D and *i*PCQ will also be completed at 4, 8, and 12 weeks. The study calendar is shown in Figure 1. The questionnaires will be completed electronically via a web-based platform. To ensure that patients complete their questionnaires in a timely manner, reminders will be sent to them via email. Paper-based questionnaires can be provided to participants who do not have access to or are less familiar with using the internet (phone call reminders).

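### Missing Data: nonmonotone missingness is named as a category but given no method, so it defaults to a weighted GEE that the plan itself describes as valid for monotone dropout

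*Protocol article*

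**What the plan says.** The Missing Data section of the protocol article sets out a sequence of decisions.

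- **Small amount missing.** The condition is "If ≤5% of the data are missing and there is no significant difference between completers and noncompleters". MCAR is then assumed, and "Under the MCAR assumption, the available case analysis performed with a GEE model yields valid estimates".
- **More than 5% missing.** First, "the missing data pattern will be categorized as monotonic (ie, no return after dropout) or nonmonotonic (ie, intermittent missing data". Next, the mechanism is studied by "examining which baseline covariates and previous measurements predict the missingness of a given outcome", where "a specific variable will be determined to be a predictor of missingness based on statistical significance and clinical plausibility".
- **Predictors found.** The data are treated as not MCAR. "This would lead to the use of the weighted generalized estimating equation (WGEE"; no other method is named.
- **Justification.** "WGEE is a valid approach for dropout missingness (monotonic missing pattern", and this pattern is said to be the usual one in longitudinal outcomes research.
- **Sensitivity analysis.** Weighted GEE is compared with available-case GEE.

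Strengths and Limitations in the Discussion repeats that weighted GEE will be used if data are not MCAR, with no condition on the pattern.

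Under Assessments and Study Calendar, EQ-5D, iPCQ and the event-count questionnaire (SAQ) fall due at weeks 4, 8 and 12, with reminders. "The questionnaires will be completed electronically via a web-based platform", or on paper where needed. The Data Collection section lists neither EQ-5D nor iPCQ at recruitment.

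**The concern.** The plan asks the analyst to decide whether the pattern is monotone, then sends both answers to the same place. For one answer, that place is a method whose stated validity does not extend to it. This is not a detail that an analysis plan would ordinarily fill in: the rule is written out and leads to a definite method.

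Intermittent gaps are plausible here. Three questionnaires are completed on separate occasions, and missing one does not end participation. The Missing Data section also counts incomplete or ambiguous EQ-5D forms and unscorable iPCQ modules as missing. One faulty form at week 8 between two good ones therefore makes a nonmonotone record.

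At stake is whether the utility and productivity coefficients are valid when response depends on earlier health. The only planned sensitivity analysis would not settle this, because under nonmonotone, non-MCAR missingness the plan supports neither of the two methods compared.

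A second, smaller problem is that significance tests choose the method, so failing to detect a difference is taken as evidence that none exists.

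**Working it through.** **1. Where each case ends up**

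| Missing | Test result | Pattern | Method stated |
|---|---|---|---|
| ≤5% | no significant difference | any | available-case GEE |
| ≤5% | significant difference | any | none |
| >5% | no predictor found | any | none; plain GEE by default |
| >5% | predictor found | monotone | weighted GEE, within its stated validity |
| >5% | predictor found | nonmonotone | weighted GEE, outside its stated validity |

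The last row is the main defect.

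**2. The plan's own figures (Sample Size)**

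68/0.17 = 400, and 400/(1 − 0.20) = 500 enrolled. Both reproduce. Planned attrition of 20% makes the >5% rows the expected ones.

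**3. How many records could be nonmonotone**

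The article gives no skip rate, so the rates here are assumptions. At each of three visits a patient still in the study drops out for good with probability h. A patient who stays skips that visit with probability s. Let a = (1 − h)(1 − s), the probability of being observed, and b = (1 − h)s, the probability of a skip while still in the study. With O observed and M missing:

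- complete record: a³
- nonmonotone: OMO = a·b·a; MOO = b·a²; MMO = b²·a; MOM = b·a·(1 − a)

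*s = 2%, h = 5%.* a = 0.931, b = 0.019. Complete 0.8070, so incomplete 0.1930 (97 of 500). Nonmonotone 0.01647 + 0.01647 + 0.00034 + 0.00122 = 0.0345 (17 of 500). Share 0.0345/0.1930 = 18%.

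*s = 5%, h = 5%.* a = 0.9025, b = 0.0475. Complete 0.7351, so incomplete 0.2649 (132 of 500). Nonmonotone 0.03869 + 0.03869 + 0.00204 + 0.00418 = 0.0836 (42 of 500). Share 0.0836/0.2649 = 32%.

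The missing share of all questionnaires is 11.5% and 14.2% respectively, so both cases fall above 5%. Cutting each record at its first gap to force a monotone pattern would discard 500 × (OMO + 2·MOO + MMO + MOM) observed questionnaires: about 25 and 61.

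The extremes are 0% nonmonotone with dropout only (h = 7.2%, 20% attrition overall) and 66% with 10% skipping and no dropout.

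**4. Loss before week 4**

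If 20% attrition is spread evenly over three intervals, the loss per interval is 1 − 0.8^(1/3) = 0.072. Then 500 × 0.072 ≈ 36 patients leave with no outcome record.

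**5. Strength of the tests (secondary point)**

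Two-sample z test, two-sided 0.05, power = Φ(d/√(1/n₁ + 1/n₂) − 1.96), with d in SD units:

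| Noncompleters vs completers | d = 0.2 | d = 0.3 | d = 0.5 |
|---|---|---|---|
| 25 vs 475 (5% of patients) | 16% | 31% | 68% |
| 100 vs 400 (20% of patients) | 43% | 77% | 99% |

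The 5% limit is not tied to a unit. Read as 5% of 1,500 questionnaires it is 75, which could touch up to 75 patients. A difference of 0.25 SD (0.05 on the utility scale at an assumed SD of 0.20) is then detected with 51% power instead of 23%. The article says that no expected SD was found, so the 0.20 is only illustrative. At 5% missing, a utility gap of 0.10 between responders and nonresponders moves the observed mean by 0.05 × 0.10 = 0.005.

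**The case against.** The strongest reply is that the plan cites monotone dropout as the usual pattern in this kind of study, and supports completion with reminders and a payment for each questionnaire. The 20% it plans for is attrition, and attrition is dropout, which weighted GEE covers. That stands against one inference a reader might draw: that planned attrition by itself pushes the study onto a pattern the method does not cover. With dropout only, no record is nonmonotone. The reply does not close the gap, because the plan provides for finding a nonmonotone pattern and then says nothing about what to do.

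Three other stronger readings also fail.

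- **Patients lost before week 4 make weighting unworkable.** They do not. Weights can be built from recruitment data such as hypoglycemia history, health care use, employment, HbA1c and complications. Weighting is weaker without an earlier outcome, but possible.
- **A severe event that causes nonresponse is invisible and biases the decrement.** Patients also keep a prospective diary, which may hold the event, although the article gives no rule for a window with a diary but no SAQ. In any case the event count is the modelled exposure. Missingness that depends only on a modelled covariate costs precision and does not by itself bias that covariate's coefficient in a correctly specified mean model. Bias needs dependence on the outcome beyond what is modelled.
- **The weak test in the MCAR branch is the main threat.** The 5% cap limits the harm there, and 20% attrition makes that branch unlikely.

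It is also fair to say that multiple imputation assumes MAR and does not cure nonresponse driven by current, unrecorded health.

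**Conclusion.** The point holds for the nonmonotone class. The plan identifies this class and assigns it, whenever predictors of missingness are found, to a method whose validity the same section ties to monotone dropout. Followed as written, the rule can give estimates that the plan's own argument does not support.

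The size depends on a skip rate that the article does not give. At 2% to 5% skipping and 5% dropout per visit, about 17 to 42 of 500 patients have nonmonotone records, 18% to 32% of those incomplete. With no skipping the problem does not arise. No bias in the coefficients has been quantified.

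The use of tests to select the method is a secondary weakness. It has little consequence at or below 5% missing. Above 5%, finding no significant predictor leaves plain GEE by default, and moderate differences could be missed (43% power for 0.2 SD at 100 versus 400). The lack of any outcome before week 4 is a limitation to state, not a separate failure of the method.

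**What to change.** Revise the missing-data rule as follows.

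1. Do not let a significance test choose the method. Report completer and noncompleter comparisons descriptively.
2. For nonmonotone missingness, use multiple imputation under MAR, then fit the planned GEE to each imputed data set and pool. The imputation model should hold outcomes at all visits, SHE and NSHE counts (with diary counts where the SAQ is missing) and baseline covariates.
3. Keep weighted GEE for monotone dropout, and available-case GEE as a sensitivity analysis.
4. Add a simple MNAR sensitivity analysis that shifts imputed outcomes by a range of deltas, since imputation under MAR does not address that case.
5. State as a limitation that patients lost before week 4 have no outcome record and are represented only through baseline covariates. Collecting EQ-5D and iPCQ at recruitment would help, but it is an optional design change.

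The cost of items 1 to 4 is revised wording and modest programming in R. The main difficulty is imputing skewed hours and event counts with care.

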#### Unmeasured Confounding

The presence of an unknown, unmeasured confounder will be explored using *E* values, which is a new standardized approach for sensitivity analysis [52,53]. For effect estimates, the *E* value is the minimum strength of association on the risk ratio scale that an unmeasured confounder would need to have with both the exposure and outcome, above and beyond the measured covariates, to fully explain the observed association of exposure with the outcome. For the 95% CI limit, the *E* value denotes the minimum strength of association on the risk ratio scale that an unmeasured confounder would need to have with both the exposure and the outcome, above and beyond the measured covariates, to shift the CI to include the null value. This sensitivity analysis will assess the robustness of the associations to unmeasured confounding.

